## Abstract

Despite advances in the understanding of cognitive dysfunction among people with epilepsy (PWE), evidence for cognitive rehabilitation in epilepsy (CoRE) remains scarce. We present the protocol of a randomized waitlist-controlled trial (ClinicalTrials.gov ID NCT05934786) of a psychological-behavioral intervention aiming to ameliorate quality of life as well as cognitive functioning in a mixed PWE sample. The study is set at Vilnius University Hospital Santaros Klinikos and will offer adult PWE six individual and two group sessions led by a certified psychologist and directed toward improving memory, attention, self-regulation, mood and quality of life. The trial is expected to address major gaps in the literature by providing novel evidence on the effectiveness of CoRE in patients with genetic generalized epilepsies, the importance of epilepsy-specific factors for the response to CoRE, the impact of CoRE on long-term memory as well as its maintenance effects.

## Introduction

1.

Epilepsy is a multifaceted chronic neurologic disorder that occurs in every hundred individuals and directly affects patients’ cognition, quality of life as well as professional and societal activities (1). Because of premature mortality, mental health and socioeconomic implications of this disorder, it is now also recognized as a global public health priority by the World Health Organization (2). Cognitive dysfunction is a major burden for people with epilepsy (PWE) as epilepsy limits their ability to remember, learn, focus, and think. It has been shown that a third of newly diagnosed PWE have subjective cognitive complaints, and up to one half perform worse than controls during objective neuropsychological evaluation (3). Epilepsy can affect various cognitive domains, such as memory or attention, with a possible increase in the level of impairment over time (4). While the problem of prevalent cognitive dysfunction is well-known and may have significant impact on quality of life and social functioning in epilepsy, studies investigating the feasibility and efficacy of cognitive rehabilitation in epilepsy (CoRE) are rare: just nine group studies were identified in the most recent systematic review (5). Importantly, most were of only moderate quality. The lack of new studies of CoRE is seen as a significant shortcoming of modern epileptology: this neglect is thought to stem from a lack in resources and a historical focus on seizure control rather than cognitive outcomes in the clinical setting (6).

We aim to conduct a novel randomized waitlist-controlled cross-over trial of an original CoRE program, assess its overall efficacity and determine factors associated with a better response to this intervention. The main hypothesis of the trial is that a combined individual and group CoRE program is effective in improving quality of life and verbal as well as visual memory in PWE.

## Methods and analysis

2.

The study protocol is reported according to the “Standard Protocol Items: Recommendations for Interventional Trials (SPIRIT)” recommendations (7, 8). The SPIRIT checklist is provided as Supplementary Table S1.

### Trial registration

2.1.

The trial was registered at ClinicalTrials.gov as study No. NCT05934786 July 7, 2023. Items of the World Health Organization Trial Registration Data Set are presented in Table 1.

**Table 1 tab1:** Items of the World Health Organization Trial Registration Data Set.

Data category	Information
Primary registry and trial identifying number:	ClinicalTrials.gov ID NCT05934786
Date of registration in primary registry	2023-07-07
Secondary identifying numbers	P-MIP-23-333
Source(s) of monetary or material support	Research Council of Lithuania, agreement No P-MIP-23-333
Primary sponsor	Vilnius University (Principal Investigator – [name])
Secondary sponsor(s)	Not applicable
Contact for public queries	[name], [contact]
Contact for scientific queries	[name], [contact]
Public title	Rehabilitation of Cognition and Psychosocial Well-being in Epilepsy
Scientific title	Rehabilitation of Cognition and Psychosocial Well-being – A Better Life with Epilepsy (ReCaP-ABLE): a randomized waitlist-controlled trial
Country of recruitment	Lithuania
Health condition studied	Epilepsy
Intervention	Behavioral: Cognitive rehabilitation Six individual one-hour therapy sessions with certified psychologists followed by two group sessions (a total of two months per patient). The intervention will consist of all parts of the Strategies-Outsourcing-Social support toolbox and include psychoeducation, lifestyle issues, coping strategies and homework.
Key inclusion and exclusion criteria	Inclusion criteria: Active epilepsy (medication for epilepsy and/or had at least one seizure in the past year). Adults (≥18 years). Lithuanian speakers. No intellectual disability. Exclusion criteria: Sensory or motor deficit preventing task completion. Epilepsy surgery planned during the project. Active non-paroxysmal comorbid disorder of the central nervous system (e.g., neurodegeneration, multiple sclerosis). Active psychiatric disorder during the past year. Psychoactive substance use (except social alcohol, tobacco and caffeine use).
Study type	Interventional randomized waitlist-controlled trial
Date of first enrollment	2024-01-01 (Estimated)
Sample size	70
Recruitment status	Not yet recruiting
Primary outcomes	Quality of life (Quality of Life in Epilepsy 31-item patient weighted version, QOLIE-31-P) 4 weeks post-intervention. Delayed verbal recall (Rey Auditory Verbal Learning Test, RAVLT) 4 weeks post-intervention. Delayed visual recall (Medical College of Georgia (MCG) Complex Figure test) 4 weeks post-intervention.
Key secondary outcomes	Symptoms of depression (Neurological Disorders Depression Inventory in Epilepsy, NDDI-E), anxiety (General Anxiety Disorder-7, GAD-7), stigma (Jacoby’s 3-item Stigma Scale).
Ethics review	Awaiting approval, Vilnius Regional Biomedical Research Ethics Committee
Completion date	2026-03-31 (estimated)
Summary results	Not applicable
Individual clinical trial participant-level data (IPD) sharing statement	No plan to share IPD

### Study setting

2.2.

The study will be set a tertiary epilepsy clinic of Vilnius University Hospital Santaros Klinikos (Vilnius, Lithuania) where patient recruitment and neuropsychological evaluation will take place. Patients will undergo CoRE at the Counseling and Training Center of the Faculty of Philosophy of Vilnius University.

### Eligibility criteria

2.3.

Patient enrolment and clinical evaluation will be done by a certified neurologist and include the following inclusion and exclusion criteria:

Inclusion criteria:

Active epilepsy (medication for epilepsy and/or had at least one seizure in the past year).Adults (≥18 years).Lithuanian speakers.No intellectual disability.

Exclusion criteria:

Sensory or motor deficit preventing task completion.Epilepsy surgery planned during the project.Active non-paroxysmal comorbid disorder of the central nervous system (e.g., neurodegeneration, multiple sclerosis).Active psychiatric disorder during the past year.Psychoactive substance use (except social alcohol, tobacco and caffeine use).

Patients with temporal lobe epilepsy as well as genetic generalized epilepsy will be enrolled.

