### Participant recruitment, allocation, and timeline

2.6.

Study participants will be invited to participate in the trial during routine outpatient visits at the epilepsy clinic. They will have either temporal lobe or genetic generalized epilepsy as confirmed by the epileptologist, according to previously collected clinical (e.g., seizure semiology, patient history), instrumental (e.g., electroencephalography, video-electroencephalography), genetic and imaging (e.g., 3T magnetic resonance imaging) data required to substantiate the diagnosis according to guidelines by the International League Against Epilepsy. After acceptance, each new participant will be randomly assigned to either the early intervention group (EIG) or the late intervention group (LIG) at the time of enrolment by using open-source software for minimization (WinPepi) based on sex, epilepsy type and seizure control. The randomization will be done, and participants assigned to one of the groups by the principal investigator. Outcome assessors and data analysts will be blinded to participant status by using concealed patient coding and instructing patients not to discuss their status during examination. The principal investigator, psychologists performing the intervention and participants themselves will not be blinded.

Both the EIG and the LIG will undergo neuropsychological assessment at three time points (Figure 2). The EIG will be tested at baseline, with two follow-ups four and sixteen weeks after the intervention which itself lasts for eight weeks. The LIG will be tested at the same time points while on waitlist. Participants assigned to the LIG will be offered the intervention after the second follow-up. Both groups will receive otherwise routine clinical care (i.e., according to individual needs and best medical practice) at the tertiary epilepsy clinic. Given the non-invasive nature of the CoRE intervention, no adverse effects are expected. Therefore, discontinuation of the intervention is expected to occur only in the case of participant dropout. Patient attrition will be minimized by thoroughly discussing the aims and procedures of the trial before enrolment as well as by accommodating to the patients’ availability and daily schedule for the weekly sessions.

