### Sample size and statistical analysis

2.7.

The target sample size of the study was calculated for a between-group interaction of a two-way repeated measures analysis of variance (ANOVA) with *f* = 0.40, *α* = 0.05, *β* = 0.95, two groups (early and late intervention), three measurement points, and 0.5 correlation between repeated measures. The resulting sample size of *n* = 58 (G*Power 3.1.9.7) was increased by 20% to *n* = 70 to account for dropouts (including the possibility of patient referral to presurgical evaluation if needed according to principles of best medical practice) and corresponded well to the mean sample size and attrition rates in previous trials (5). This sample size is deemed achievable as the trial will be conducted in a large university hospital covering tertiary epilepsy care services for approximately 1.4 million of inhabitants and include a group of PWE composed of patients with both TLE and GGE.

The efficacy of the intervention will be defined as statistically significant improvement on one of the primary outcomes (quality of life or delayed memory), tested with a repeated-measures between-factors analysis of variance (ANOVA) in the EIG as compared to the LIG. For secondary analyses, dynamic changes of other outcome measures will be tested, respectively, by using ANOVA or ANCOVA. The association between demographic and clinical variables with study endpoints will be conducted by means of linear and ordinal regression modeling. Subgroup analyses are planned to be conducted based on sex, education status, professional status, epilepsy type, laterality and lesionality. In case of missing data, multiple imputation will be used in sensitivity analysis.

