## Conclusion

6.

In this protocol we outlined a plan to conduct a randomized waitlist-controlled trial exploring the effects of a psychological-behavioral cognitive rehabilitation program on the quality of life and memory function in adults with epilepsy. This trial is an attempt to demonstrate feasibility and test the effectiveness of CoRE in a mixed PWE sample as well as to provide additional evidence about the target population for CoRE and the determinants of its effects. We believe that such an initiative will help further translate the experience that has emerged from neuropsychological evaluation in epilepsy to non-invasive add-on rehabilitation programs addressing burdensome cognitive issues among PWE.

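### The response analyses named in the article leave out baseline cognition, although enrolment is unselected for cognitive deficit and finding who responds is a stated aim

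*Protocol article*

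**What the plan says.** **Entry.** The Eligibility criteria section admits adults who speak Lithuanian and have "Active epilepsy (medication for epilepsy and/or had at least one seizure in the past year". The only criterion about cognitive level is "No intellectual disability", which removes the most impaired and requires no impairment in anyone else. On epilepsy type, "Patients with temporal lobe epilepsy as well as genetic generalized epilepsy will be enrolled". Table 1 repeats the listed inclusion and exclusion criteria.

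**Background.** The Introduction reports that "a third of newly diagnosed PWE have subjective cognitive complaints, and up to one half perform worse than controls during objective neuropsychological evaluation".

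**Aims.** The Introduction sets out to find factors that go with a better response. The Conclusion adds evidence on the target population and on what determines the effect, and hopes to support "non-invasive add-on rehabilitation programs addressing burdensome cognitive issues among PWE".

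**Planned analyses of response.** Section 2.7 states: "Subgroup analyses are planned to be conducted based on sex, education status, professional status, epilepsy type, laterality and lesionality". It adds: "The association between demographic and clinical variables with study endpoints will be conducted by means of linear and ordinal regression modeling". The demographic and clinical variables are listed at the end of section 2.5 and include no cognitive score. Allocation uses "minimization (WinPepi) based on sex, epilepsy type and seizure control".

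**Data.** Both groups have a neuropsychological assessment at baseline. The verbal and visual recall tests and 0-10 ratings of subjective cognition are among the trial's measures.

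**The concern.** A treated, seizure-free patient with normal memory and no complaint is eligible. Such a patient may have less to gain on a 15-word list or a figure recall than one with a deficit, so the average recall effect may depend on how many enrolled patients have a deficit. If the recall results are weak, two explanations compete: the strategies do not help memory, or they help mainly those with a deficit and there were too few of them. Baseline memory bears directly on that choice, and it is not among the factors the article names for studying response.

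What is at stake is the secondary aim. The trial could report on sex, education, profession, epilepsy type, laterality and lesionality, yet have nothing pre-specified on the characteristic closest to need. A baseline-score analysis chosen after a disappointing result would carry much less weight than one named beforehand.

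**Working it through.** **1. Where baseline cognition could have entered**

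| Place in the article | Factors named | Baseline cognition? |
|---|---|---|
| Eligibility (2.3) | epilepsy activity, age, language, no intellectual disability, exclusions | no deficit or complaint required |
| Minimization (2.6) | sex, epilepsy type, seizure control | no |
| Subgroups (2.7) | sex, education, profession, epilepsy type, laterality, lesionality | no |
| Regression variables (listed in 2.5) | demographic and clinical items | no |
| ANOVA/ANCOVA for secondary outcomes (2.7) | covariates not named | not stated |

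In the primary repeated-measures ANOVA the baseline score is one of three responses, not a modifier of the group effect.

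**2. The plan's own sample size**

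Inputs from section 2.7: f = 0.40, α = 0.05, target power 0.95 (printed as β), two groups, m = 3 measurements, correlation ρ = 0.5, N = 58.

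Between-factors F test: λ = f²·N·m / (1 + (m − 1)ρ), with 1 and N − 2 degrees of freedom.

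λ = 0.16 × 58 × 3 / 2 = 13.92, power 0.956. N = 56 gives 0.9495, so 58 is reproduced exactly.

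Section 2.7 calls the effect an interaction. The within-between interaction formula, λ = f²·N·m / (1 − ρ), gives N = 18, so it is not the calculation behind 58.

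**3. Illustration of dilution**

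Assumption: f = 0.40 holds only in patients with a deficit, who make up a share p, and the others gain nothing. The average effect is then f = 0.40p. At N = 58, λ = 87f²:

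| Share p | f | λ | Power |
|---|---|---|---|
| 1 | 0.40 | 13.92 | 0.956 |
| 3/4 | 0.30 | 7.83 | 0.79 |
| 1/2 | 0.20 | 3.48 | 0.45 |
| 1/3 | 0.133 | 1.55 | 0.23 |

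If half have a deficit and the rest gain one-third as much, f = 0.5 × 0.40 + 0.5 × 0.133 = 0.267 and power is 0.69.

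One-half and one-third echo the Introduction's figures for newly diagnosed patients; three-quarters allows for a more impaired clinic population. None is an estimate for this trial. The result also depends on the test: the interaction formula at f = 0.20 and N = 58 would give 0.92.

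**4. What a moderator analysis could deliver**

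Same assumption, with d = 2f = 0.80 in impaired patients and 0 in the others. The mean of three measurements has SD √((1 + 2 × 0.5)/3) = 0.816. The interaction's standard error is 0.816 × √(4/(58p) + 4/(58(1 − p))).

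- p = 1/2: SE = 0.429, 0.80/0.429 = 1.87, power Φ(1.87 − 1.96) ≈ 0.46.
- p = 1/3: SE = 0.455, 0.80/0.455 = 1.76, power Φ(1.76 − 1.96) ≈ 0.42.

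This treats impairment as yes/no and uses a normal approximation. It indicates the order of size for a continuous term, not its exact power.

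**The case against.** **Broad enrolment is deliberate.** The article describes a mixed sample and discusses heterogeneity in epilepsy type. This stands: nothing is misstated, and eligibility need not change. The Limitations section does not, however, mention heterogeneity in cognitive need.

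**The programme is wider than memory.** It also targets mood, self-regulation and quality of life. QOLIE-31-P was chosen to catch effects outside objective cognition, and efficacy may rest on one primary outcome. This stands too, and confines the point mainly to the two recall outcomes.

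**The shares are uncertain.** The Introduction's figures concern newly diagnosed patients, whereas this is a tertiary clinic. The article also says impairment may grow over time and is frequent in genetic generalized epilepsy. The programme teaches strategies, which need not require a deficit. All this is fair, so the figures in the working are illustrations only.

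**The subgroup list may not be complete.** The Discussion also mentions adjustment for anxiety and depression, and metacognition as a possible explanation of response. A fuller plan may add more. But where the article lists its subgroups and variables it does so explicitly, and the factor nearest its own aim is absent from all of them.

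**The added test is weak.** Correct: power of about 0.42 to 0.46 means that a null interaction leaves the question open. The six planned subgroups face the same small sample and are less directly tied to need.

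A reader might infer that a diluted effect could never be told from an ineffective programme. The documents do not support that: baseline scores exist in both groups, so the analysis remains possible. It is simply not among those stated.

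**Conclusion.** The point holds as a gap between aim and analysis. The trial enrols patients unselected for cognitive complaint or deficit and wants to learn who responds, yet no analysis stated in the article relates the recall effect to baseline cognition.

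Its size cannot be fixed from the documents. Power on a recall outcome would be 0.79 if three-quarters of patients can respond and 0.45 if half can, provided that f = 0.40 belongs to impaired patients only and the rest gain nothing. A reader might conclude that the trial is underpowered. That does not follow: section 2.7 sets f = 0.40 for the whole sample, nothing says it came from impaired patients, and N = 58 reproduces on that basis.

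This is a worthwhile low-cost improvement, not an error in eligibility or sample size.

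**What to change.** Leave eligibility as it is. In section 2.7:

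- For each memory outcome, name its own baseline score as a continuous covariate and as a pre-specified exploratory effect modifier (group by baseline). In that model use the follow-up scores as the response, so that baseline does not stand on both sides.
- Report the estimated group effect, with confidence interval, at average baseline and at a low value fixed in advance.
- Report the distribution of baseline scores by group, so that readers can see how much deficit was enrolled.
- Word the main conclusion as applying to patients with temporal lobe or genetic generalized epilepsy unselected for cognitive impairment.
- Optionally, add a similar term for QOLIE-31-P using the baseline 0-10 subjective cognition rating.

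**Cost:** wording and analysis time only, with no new visits, patients or measures. The downside is one more exploratory interaction per memory outcome, with low power. The plan should say that a null interaction would not rule out a difference in response by baseline memory.

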### Intervention

2.4.

The intervention will consist of an eight-week-long psychological-behavioral program with six weekly individual sessions of 60 min followed by two group sessions. The group sessions are also planned to last 60 min and include five to seven PWE. The intervention will include all parts of the Strategies-Outsourcing-Social support toolbox (6) and involve psychoeducation, lifestyle issues, coping strategies, and homework (Box 1). The sessions will be led by certified psychologists, all of them will be trained by one leading specialist to ensure standardization. Patients will participate in group sessions led by the same specialist who provided individual sessions. There are no expected changes or modifications to the structure of the intervention upon its roll-out.

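### The early arm is clustered by psychologist and therapy group, but the primary ANOVA and the sample size treat patients as independent; if outcomes correlate within clusters, standard errors are too small

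*Protocol article*

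**What the plan says.** All points are from the protocol article.

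- **Delivery (Intervention).** The program has "six weekly individual sessions of 60 min followed by two group sessions". On staffing: "The sessions will be led by certified psychologists, all of them will be trained by one leading specialist to ensure standardization". On continuity: "Patients will participate in group sessions led by the same specialist who provided individual sessions". On group size: "The group sessions are also planned to last 60 min and include five to seven PWE". Each therapy group therefore sits within one psychologist, who gives a patient all eight sessions.
- **Control (Participant recruitment, allocation, and timeline).** Allocation is by individual minimization. The late intervention group (LIG) is assessed three times while waiting: "Participants assigned to the LIG will be offered the intervention after the second follow-up".
- **Analysis (Sample size and statistical analysis).** Efficacy is "tested with a repeated-measures between-factors analysis of variance (ANOVA) in the EIG as compared to the LIG".
- **Sample size (same section).** The calculation uses "with *f* = 0.40, *α* = 0.05, *β* = 0.95, two groups (early and late intervention), three measurement points", with a within-patient correlation of 0.5. It gives 58, raised to 70 for dropout. That correlation is the only dependence mentioned. Psychologist, therapy group, ICC and design effect do not appear.

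**The concern.** This is a partially nested design: patients in the early intervention group (EIG) belong to clusters during the comparison, and LIG patients do not. Patients who share a psychologist or a therapy group may end up with similar outcomes. A positive ICC is plausible here because the two group sessions work on social support, and quality of life is both a session topic and a primary outcome.

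A positive ICC makes the variance of the EIG mean larger than the ANOVA assumes. Confidence intervals are then too narrow and P values too small. The planned power is also overstated, because the sample size carries no allowance for clustering.

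**Working it through.** **1. Reproduce the plan's figure.** Inputs: f = 0.40, α = 0.05, power 0.95 (the article prints this as β), two groups, m = 3 visits, ρ = 0.5. For the between-factors test:

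λ = f²·N·m / (1 + (m − 1)ρ) = 0.16 × 3N / 2 = 0.24N, with 1 and N − 2 degrees of freedom.

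N = 56 gives power 0.9495 and N = 58 gives 0.956, so 58 reproduces. Then 58 × 1.2 = 69.6, or 70. Patients are independent throughout, and the 20% is for dropout only.

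**2. Cluster sizes.** Assuming 1:1 allocation, 70 patients give 35 in the EIG, or about six groups of about six. The group size comes from the document. The number of psychologists does not; three would give a caseload of about 12 (35 / 3 = 11.7).

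**3. Effect on the standard error and the test.** With k patients per cluster, in the EIG only:

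- Design effect: DE = 1 + (k − 1)·ICC
- True SE / ANOVA SE: R = √((DE + 1)/2)
- Type I error: 2·P(Z > 1.96/R)

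| Cluster | ICC | DE | R | Type I error |
|---|---|---|---|---|
| Group, k = 6 | 0.02 | 1.10 | 1.025 | 5.6% |
| Group, k = 6 | 0.05 | 1.25 | 1.061 | 6.5% |
| Group, k = 6 | 0.10 | 1.50 | 1.118 | 8.0% |
| Psychologist, k = 12 (assumed) | 0.02 | 1.22 | 1.054 | 6.3% |
| Psychologist, k = 12 (assumed) | 0.05 | 1.55 | 1.129 | 8.3% |
| Psychologist, k = 12 (assumed) | 0.10 | 2.10 | 1.245 | 11.5% |

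**4. Check by simulation.** These are unadjusted two-arm comparisons with zero mean effect, 29 or 35 per arm and 200,000 runs per scenario. Groups of about six gave 5.5–5.6%, 6.4–6.5% and 7.8–7.9% at ICC 0.02, 0.05 and 0.10. Three psychologists gave 6.0–6.2%, 7.6–8.3% and 10.2–11.5%. At ICC = 0 the test held 5%.

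A second simulation ran the three-visit ANOVA with clustering only at the two post-intervention visits (40,000 runs, five or six groups). The group-by-time interaction rejected 5.3–5.6%, 6.2–6.5% and 7.8–7.9% of the time. The between-group main effect rejected 5.4%, 6.0–6.1% and 6.8–6.9%. The main effect is inflated less because it averages in the unclustered baseline.

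**5. Effect on power.** At N = 58 with groups of six, dividing λ = 13.92 by R² gives power 0.947, 0.933 and 0.906 at ICC 0.02, 0.05 and 0.10. The N that restores the planned power is 58 × R², which rounds up to 61, 66 and 73. This treats all three visits as clustered, so it is slightly pessimistic.

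**The case against.** A reader might infer that the type I error certainly exceeds 5%. The document does not support that, for two reasons.

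- The result needs ICC > 0, and no ICC is given. Common training and a fixed session plan may keep the ICC low, only two of the eight sessions are in groups, and two of the three primary measures are memory tests scored by blinded assessors. At ICC 0.02 with groups of six the excess is about half a percentage point.
- It needs a particular null hypothesis. Allocation is individual, so if the program affects nobody, shared delivery adds no variance and the test keeps about 5%. Inflation arises when the mean effect is zero but groups or psychologists differ in effect or case mix. If inference is limited to the psychologists in this trial, psychologist can be a fixed effect and that part of the inflation disappears.

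A reader might also infer that one psychologist treats the whole arm. The article says psychologists, in the plural. The caseload of 12 is an assumption; only the group size is documented.

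All of this stands, and it limits the size and certainty of the point. It does not remove it, because training and a session plan cannot rule out dependence within a group.

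The last objection is that an analysis plan, not shown, could add the missing term. It could. But the article already names the primary test and sizes the trial on it, and both assume independence.

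**Conclusion.** The point holds in conditional form. The delivery model clusters the EIG only, and the named ANOVA and the n = 58 calculation ignore that. For any positive ICC the unadjusted standard error is too small. With the documented group size the understatement is modest: the true standard error is about 2–12% larger for ICC 0.02–0.10. Type I error is then 5.6–8.0% under a null of zero mean effect with real differences between groups. It is larger if psychologists also differ, but that rests on an assumed caseload.

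The trial should deal with this before analysis. The document does not show that the result would be invalid without it.

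**What to change.** 1. Make sure psychologist and therapy group are recorded for each participant. The article's list of collected data names neither, although a condensed list does not show that they go unrecorded.
2. Analyse the primary outcomes with a partially nested mixed model: a therapy-group random effect in the EIG only, with Kenward-Roger or Satterthwaite degrees of freedom.
3. There are probably too few psychologists to estimate a psychologist variance. Report the primary result over a range of fixed psychologist ICCs, for example 0 to 0.10, as a sensitivity analysis.
4. State that the planned power of 0.95 assumes ICC = 0.

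**Cost.** Two data fields, some analysis text and wider intervals. With 35 per arm, six groups and ICC 0.05, the EIG design effect is 1 + (35/6 − 1) × 0.05 = 1.242. Satterthwaite df = (1.242 + 1)² / (1.242²/5 + 1/34) ≈ 15. The interval is 1.059 × 2.133 / 1.995 = 1.13 times as wide as the unadjusted one. At ICC 0.02 it is about 9% wider and at 0.10 about 21% wider, so roughly 10–20%.

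An estimated psychologist effect would cost far more at ICC 0.05: 42% wider with three psychologists (df about 5) and 2.2 times as wide with two (df about 2.4). That is why step 3 fixes the psychologist ICC instead of estimating it.
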